## Abstract

Although the effectiveness of cardiac rehabilitation (CR) programs in secondary prevention is well-recognized, there is a lack of studies exploring the potential of mobile health to enhance educational interventions within CR. The objective is to assess the impact of a structured WhatsApp-assisted health educational intervention, in conjunction with the usual care, compared to the usual care alone among participants enrolled in a CR program. The trial will recruit 32 participants enrolled in a CR program, who will be randomly assigned to a structured WhatsApp-assisted health educational intervention plus usual care or usual care alone group. The intervention will span 4 weeks, with assessments at baseline, 4 weeks, and 3, 6, and 12 months. The primary outcome measure is the cardiovascular risk factors knowledge score. Secondary outcomes include physical activity levels, anxiety and depression, and quality of life. Expected results include improved knowledge of cardiovascular risk factors, increased physical activity levels, and better mental health outcomes in the intervention group. Additionally, an enhancement in the overall quality of life is anticipated. These findings are expected to underscore the value of integrating mHealth with traditional CR methods, potentially shaping future approaches in chronic disease management and prevention.

## 1. Introduction

Cardiac diseases are one of the leading causes of mortality worldwide [1]. Specifically, ischemic cardiopathy was responsible for 18.6 million deaths in 2019 [1]. Cardiac rehabilitation (CR) programs, defined as multidisciplinary interventions involving exercise and education, over the last decade have emerged as a valuable secondary prevention strategy to promote lifestyle changes [2], improve cardiopulmonary fitness [3], reduce the risk of mortality [4,5], and enhance mental health [6].

The scientific literature has demonstrated that educational interventions targeting patients living with cardiovascular diseases have a positive effect on disease knowledge, behavioral changes, and health-related quality of life and decrease the recurrence of cardiac events [7,8]. Moreover, different guidelines propose specific topics that should be taught to patients with cardiomyopathies [8,9]. However, there is a lack of consensus about the most effective method for delivering this educational content effectively [10,11,12].

Mobile health (mHealth) presents itself as a versatile solution, offering an alternative to traditional in-person interventions or enhancing these visits by minimizing barriers such as distance, cost, and time [13,14,15]. This innovative approach leverages technology to provide accessible healthcare options, bridging gaps that often exist in conventional healthcare settings [13,14]. This is particularly relevant in the context of CR, where the use of technology has been rapidly expanding [12]. Among various mHealth tools, WhatsApp, a free and widely used instant messaging app, shows promise and potential in health education [16]. Its effectiveness has been demonstrated in delivering educational content on topics like tobacco consumption and cardiovascular risk to patients with heart conditions, yielding positive results in patient outcomes [17].

Studies such as those conducted by Arantes et al. [10] and Pinzon et al. [18] have highlighted the significant benefits of incorporating technology into CR programs. These benefits include improved patient adherence to CR programs, reduced anxiety, facilitated recovery processes, and delayed disease progression. Additionally, the use of educational interventions in CR has been shown to increase patients’ knowledge and awareness of risk factors and lifestyle impacts [17,19]. However, despite the growing trend in utilizing mHealth for educational purposes in CR [20], especially post-COVID-19 pandemic [21], research focusing on the Latin American region remains limited [22].

In Colombia, WhatsApp has emerged as the predominant communication platform among the adult population. Its extensive adoption is evident, with statistics showing that eight out of every ten Colombians use WhatsApp as their primary mode of communication [23]. This widespread usage positions WhatsApp as an ideal medium for effective and extensive engagement, particularly in the realm of healthcare and patient education.

Given this context, the objective of this research is to explore the potential of WhatsApp as a tool for enhancing CR programs. Specifically, this study aims to assess the impact of a structured WhatsApp-assisted health educational intervention, in conjunction with the usual care, on improving participants’ knowledge of cardiovascular risk factors, their physical activity levels, and mental health parameters such as anxiety and depression. Additionally, this study will evaluate the intervention’s effect on the overall quality of life of participants attending a CR program. These assessments will be conducted immediately following the intervention and then again 12 months later, allowing for a comparison of the long-term effects of the WhatsApp-assisted approach versus the usual care alone. This research seeks to provide valuable insights into the efficacy of integrating mobile health technology with traditional care methods in CR settings.

## 2. Experimental Design

### 2.1. Study Design

The study design is a single-blinded, two-arm, parallel, randomized controlled trial comparing the effects of a WhatsApp-assisted health educational intervention to those of the usual care on knowledge of cardiovascular risk factors, physical activity levels, and mental health in adults attending a CR program.

### 2.2. The Theoretical Basis of Our Work

This study is supported by the transtheoretical model of change (TTM) developed by Prochaska and DiClemente [24] and the andragogy that describes the adult learner [24]. The TTM can be used to determine individuals’ intention to change according to stages including precontemplation (the new behavior is not considered), contemplation (the new behavior is contemplated but not acted upon), preparation (efforts are made to prepare for adopting the new behavior), action (the initial behavior change is made), and maintenance (the new behavior is maintained over time). The andragogy [24] theory has five assumptions: somebody (1) has an independent self-concept and can direct their learning, (2) has accumulated a reservoir of life experiences that is a rich resource for learning, (3) has learning needs closely related to changing social roles, (4) is problem-centered and interested in the immediate application of knowledge, and (5) is motivated to learn by internal rather than external factors [25].

### 2.3. Study Setting

Participants will be recruited in Bucaramanga, Colombia, which is ranked the city with the ninth-largest population in the country, with 607,428 people according to the 2019 National Statistics Projections. Participants will be selected from the outpatient clinic “Profesionales de la Salud y Cia LTDA” located in a tertiary care center.

### 2.4. Participants

Eligible individuals must be over 18 years of age, possess a smartphone with a data plan or Wi-Fi access, and have proficiency in using the WhatsApp application, including basic skills to read, write, and interact with content on the platform. Additionally, they should be prescribed at least 20 CR sessions. Exclusion criteria include participation in any CR program in the past, a prior diagnosis of depression or anxiety, cognitive impairment as indicated by a Mini-Mental Test score below 25, institutionalization, severe co-morbidities contraindicating CR, or experiencing severe surgical complications such as a general stroke with severe disability.

## 3. Procedure

### 3.1. Recruitment

All patients seeking appointments at the outpatient clinic ‘Profesionales de la Salud y Cia LTDA’ for CR will undergo screening to identify those who meet these criteria. Those who qualify will be provided with detailed study information, and informed consent will be obtained before participation.

### 3.2. Randomization and Masking

Randomization will be conducted after baseline assessment. The participants will be randomized into one of the two groups: WhatsApp-assisted health educational intervention with the usual care (intervention group) or the usual care (control group). We will employ permuted block randomization for participant allocation. This approach involves generating a randomized sequence using varying block sizes to assign participants to different treatment groups. This method ensures balanced group sizes and minimizes selection bias. To maintain methodological quality and safeguard this study’s integrity, an allocation concealment strategy will be utilized involving the use of sealed opaque envelopes. These envelopes will be sequentially numbered and prepared by an individual not involved in the enrollment or assessment of participants. They will only be opened by personnel separate from the envelope preparation and assessment processes, thereby maintaining the concealment of the allocation sequence until assignment and preventing potential biases. Evaluators and data analysts will be masked to treatment allocation; however, participants will not be masked. Furthermore, the evaluator responsible for initial assessments will be blinded to group assignments, ensuring an unbiased evaluation process. The therapist administering the intervention via WhatsApp will be different from the one providing usual care, reinforcing the independence of treatment delivery from the assessment process. This structure is designed to maintain the integrity of the study by separating roles and concealing group assignments from those conducting assessments. All team members involved in this study were trained on the importance of maintaining blinding and will be regularly monitored for compliance.

### 3.3. Follow-Up

Post-assessments will be conducted immediately after the intervention (4 weeks), as well as at 3-, 6-, and 12-month follow-ups by telephone. See the flowchart of this study in Figure 1.

### 3.4. Interventions

The WhatsApp-assisted intervention plus usual care group (16 participants) and the usual care alone group (16 participants) will receive supervised exercise sessions and an in-person educational intervention provided by the “Profesionales de la Salud” Rehabilitation center.

#### 3.4.1. Usual Care

Supervised exercise sessions

Participants will receive five 45-min sessions of exercise per week over 4 to 6 weeks. The number of weeks depends on the number of sessions prescribed by the cardiologist. Each session will include 5 min of warm-up and 30 min of moderate-intensity exercise on the treadmill or recumbent bike. These exercises are designed by a physiotherapist and involve a Borg scale effort perception of between 3 and 6, targeting 50% to 70% of the maximum heart rate. Additionally, the sessions will include 10 min of endurance exercise using elastic bands offering varying resistance levels, to be selected according to the participant’s progress, with each exercise performed for 8–10 repetitions. The sessions will conclude with a cooldown phase of 5 min. The sessions will be conducted in an outpatient clinic located in a tertiary care center.

In-person educational intervention

Participants will be engaged in twice-weekly, 10 min informational sessions conducted in person by a registered physical therapist (PT) over a period of 4 to 6 weeks according to the cardiologist’s prescription. To ensure personalized attention and effective learning, each session will be conducted in small groups, limited to a maximum of 10 participants. Additionally, patients will be provided with informative flyers that offer detailed insights into their specific cardiac conditions, enhancing their understanding and engagement with their healthcare journey.

#### 3.4.2. The WhatsApp-Assisted Intervention

In addition to the usual care, the intervention group will receive a structured educational intervention delivered by daily WhatsApp messages including videos, images, and/or podcasts, explicitly designed for this study. The maximum number of participants in each WhatsApp-assisted group will be four, and, in total, there will be four groups. The WhatsApp intervention will be delivered concurrently over the same 4-week period for those with a 4-week exercise intervention and in the first 4 weeks for those with a 6-week exercise intervention. The in-person educational intervention and the WhatsApp-assisted intervention will be simultaneously conducted over the same 4-week period, ensuring a cohesive and integrated approach to patient care.

In the WhatsApp-assisted intervention, there will be a weekly theme as follows: hypertension, diabetes mellitus, smoking, and dyslipidemia. A WhatsApp message will be sent once a day for four weeks from Monday to Friday, at 8:00 AM. Participants will receive a message and an image of the physiopathology related to the weekly theme on Monday, a message and an image with relevant medication information on Tuesday, an image and a podcast about nutritional recommendations on Wednesday, a video of physical activity on Thursday, and an image with motivational phrases on Friday. In addition, every day after sending the message, a member of the research team will be available to answer questions from participants regarding the information provided.

The main functions of the WhatsApp-assisted intervention will be to enhance understanding and facilitate substantial lifestyle modifications in cardiac rehabilitation patients by providing tailored guidance on disease management, pharmacological treatments, nutrition, and physical activity through multimedia resources. The Knowing competencies will focus on educating patients about their condition and its possible repercussions, promoting awareness of heart-healthy dietary choices, emphasizing the importance of physical activity for cardiac health, and identifying risk factors linked to poor lifestyle habits. This foundational knowledge is crucial for patients to understand the why behind the recommended changes, making it easier for them to commit to these adjustments. The Being competencies concentrate on the patient’s self-awareness and reflection on their lifestyle choices. Patients are encouraged to recognize the impact of their decisions on their rehabilitation journey. This aspect underscores the importance of personal responsibility and the realization that their choices can lead to either positive or negative outcomes in their recovery process. The Doing competencies are about translating knowledge and awareness into action. Patients are expected to adhere to healthy eating recommendations, develop the ability to set practical physical activity goals, and engage in educational programs to acquire the tools needed for lifestyle modification. Through this structured approach, the WhatsApp-assisted intervention seeks not only to inform but also to transform cardiac rehabilitation patients, guiding them towards healthier lifestyle choices that support their recovery and long-term wellbeing.

### 3.5. Development of WhatsApp Messages

The development of WhatsApp messages will be a critical component. The authors will follow the steps outlined by the Pan American Health Organization (PAHO) for the creation of edu-communicative material [26]. This process will ensure that the educational content is not only informative but also engaging and tailored to the specific needs of the participants.

#### 3.5.1. Defining the Health Situation

Initially, the team will define the current health situation, focusing on the prevalence and impact of cardiovascular diseases. This step will involve a thorough analysis of the latest research and statistics to ensure that the content is relevant and up-to-date.

#### 3.5.2. Identifying Educational Needs

The next step will involve identifying the educational needs of the participants. This will be achieved through interviews with potential participants and healthcare professionals. The goal is to understand the gaps in knowledge and misconceptions about cardiovascular health, rehabilitation, and lifestyle changes.

#### 3.5.3. Strategic Definition of Content

Once the educational needs are identified, the team will strategically define the content to be included in the WhatsApp messages. This content will be designed to address the identified needs in an interactive and engaging manner.

#### 3.5.4. Strategic Plan for Production

The team will use free software tools such as Canva, Powtoon, Movie Maker, and PowerPoint to create a total of 27 pieces, including images, pop quizzes, and videos. These tools will enable the creation of visually appealing and easy-to-understand content.

#### 3.5.5. Design and Validation

Once the initial designs are complete, they will undergo a validation process. This process will involve presenting the material to seven health science experts and six users from a program to gather feedback. Their insights will be invaluable in refining the content to ensure it is effective and resonates with the audience.

### 3.6. Adherence to the Intervention

Adherence to the supervised exercise sessions and the in-person educational intervention will be monitored by an attendance signature. In addition, a member of the research team will check the WhatsApp read receipts through the WhatsApp option “read by” every day at 8 PM from Monday to Friday.

### 3.7. Providers

The usual care will not be provided by the research group, but will be delivered by healthcare providers at the rehabilitation center. The WhatsApp intervention will be delivered by two physiotherapists. One of them is specialized in CR, completed a master’s in education, and has 12 years of clinical experience in CR. The second physiotherapist is specialized in neurorehabilitation, completed a master’s in physiotherapy, and has 14 years of clinical experience in CR.

### 3.8. Primary Outcome

Cardiovascular Risk Factors Knowledge (CRFK) Score: Specifically designed and validated for this study, the knowledge questionnaire (Supplementary Materials) comprises 18 items across four disease-based dimensions: hypertension (4 items), diabetes mellitus (5 items), smoking (4 items), and dyslipidemia (5 items). Each item, structured as a statement, invites respondents to self-assess their knowledge using a five-point Likert scale, ranging from ‘No Knowledge’ (1) to ‘Extensive Knowledge’ (5). The knowledge score for each disease dimension is the average of its corresponding items. Additionally, through these 18 questions, four thematic dimensions are covered: pathophysiology (4 items), pharmacology (4 items), nutrition (6 items), and physical activity (4 items) (see Supplementary Materials). Each thematic dimension is scored from 1 to 5, where a higher score reflects more extensive understanding.

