### 3.11. Statistical Analysis

Descriptive statistics such as means and standard deviations or medians and interquartile ranges for continuous variables and frequency tables for categorical variables will be used.

The bivariate analysis will be carried out to evaluate the differences in the variables measured within each group and between the study groups using parametric or non-parametric tests.

To evaluate the changes through follow-up, a repeated-measures analysis of variance will be applied if data follow a normal distribution, or a non-parametric variance analysis (ATS) if data do not follow a normal distribution [33]. Multivariable generalized estimating equation (GEE) models [34] will be applied to determine the effects of group, time, and the interaction between group and time on physical activity levels.

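### The single primary CRFK score has no overall scoring rule, primary visit or deciding contrast, so the stated 5% level and 80% power attach to no defined comparison

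*Protocol article*

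**What the plan says.** **Outcome.** The Abstract names a single measure: "The primary outcome measure is the cardiovascular risk factors knowledge score". Section 3.8 is the only place where the article describes how it is scored. For the disease grouping (hypertension 4 items, diabetes 5, smoking 4, dyslipidemia 5) the rule is "The knowledge score for each disease dimension is the average of its corresponding items". The same 18 items are then regrouped: "four thematic dimensions are covered: pathophysiology (4 items), pharmacology (4 items), nutrition (6 items), and physical activity (4 items"). For these, "Each thematic dimension is scored from 1 to 5, where a higher score reflects more extensive understanding". No total or overall mean is given.

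**Timing.** Section 3.3 sets four post-baseline assessments: "Post-assessments will be conducted immediately after the intervention (4 weeks), as well as at 3-, 6-, and 12-month follow-ups by telephone". The Introduction mentions only two of them: "These assessments will be conducted immediately following the intervention and then again 12 months later". Neither section calls a visit primary.

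**Analysis.** Section 3.11 plans bivariate tests to "evaluate the differences in the variables measured within each group and between the study groups using parametric or non-parametric tests". It adds a repeated-measures analysis of variance, or a non-parametric counterpart, for change over follow-up. The one model with an explicit group-by-time interaction, the GEE, is assigned to physical activity, which is a secondary outcome.

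**Sample size.** Section 3.10 assumes a single comparison of means on the main outcome, with 5% significance, 80% power and 1:1 allocation, doubled for losses to 16 per group. It does not say which score or visit that comparison uses.

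**The concern.** A significance level and a power describe one specified test. To identify that test, a reader needs the variable, the time and the contrast. The article leaves all three open for its primary outcome, although its Abstract and sample-size section write as if all three were settled.

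The scoring rule yields several scores, the schedule yields several visits, and the analysis section yields several kinds of test. If the choice among them is made after the data are seen, the chance of a nominally significant knowledge result under no effect is larger than 5%. A reader of the results could not tell a planned primary finding from a selected one. The trial has 32 participants who are not masked and who rate their own knowledge, so a positive claim needs a clearly pre-specified test.

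**Working it through.** **1. Scores defined.** Disease grouping: 4 + 5 + 4 + 5 = 18 items, four scores. Thematic grouping: 4 + 4 + 6 + 4 = 18 items, four scores. Both groupings use the full questionnaire, so there are eight overlapping scores and no overall one.

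**2. The plan's own sample size.** The stated 16 per group cannot be reproduced, because section 3.10 gives neither the mean difference nor the standard deviation that it took from a cited study. Solving backwards: 16 / 2 = 8 per group before doubling. At two-sided 5% (sidedness is not stated, so this is an assumption) and 80% power, the normal formula gives a standardised difference d = (1.960 + 0.842) × √(2/8) = 1.40. The t-test version gives 1.51. The article does not say on which score, or at which visit, a difference of that size is expected.

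**3. False-positive risk if several results could count.** The documents give no correlations, so these are assumed. The model has no true effect, 16 per arm, t-tests at two-sided 5%, and the same correlation r between dimensions and between visits.

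- Independent tests, as a reference ceiling: 1 − 0.95^4 = 18.5% for four tests.
- Four correlated tests, simulated with 20,000 runs. This covers both one total at four visits and four dimensions at one visit, since under a common r they are the same calculation.
- Four disease dimensions at four visits, 16 tests, from the same simulation.

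| r | Four tests | Sixteen tests |
|---|---|---|
| 0.5 | 16% | 43% |
| 0.6 | 15% | 38% |
| 0.7 | 13% | 32% |

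A separate run of 4,000 gave 44%, 38% and 30% for the sixteen tests, hence the range 30–44%. At r = 0.8 the sixteen-test figure falls to about 25%.

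**4. After the fix.** One score, one time point and one between-arm contrast give a type I error of 5% by construction.

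**The case against.** The strongest reply is that one overall score was plainly intended. The Abstract and section 3.8 use the singular, section 3.10 sizes one comparison, and section 4 states the expectation for knowledge as intervention against control. Section 3.8 also points to Supplementary Materials, which were not available here and may define a total. This largely stands as a reading of intent, and it settles the direction of the contrast: the within-group tests are not put forward as evidence of success. It does not supply the score, the visit or the deciding test in the article itself.

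A second reply is that the repeated-measures analysis pools the visits into one model. That would indeed reduce the visit multiplicity. However, section 3.11 does not say that this model decides the primary outcome, does not name the effect that would decide it, and lists bivariate tests beside it.

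A third reply is that multiplicity rules are commonly left to a statistical analysis plan. That is accepted, and the absence of such a rule is not the complaint. The complaint is that the primary endpoint as described does not match the single comparison on which the trial is sized.

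A reader might go further and infer that the plan contains 8 scores × 4 visits = 32 primary tests, each at 5%. The documents do not support that. Nothing makes a dimension score a success criterion, and 5% appears only in the sample-size section. A reader might also argue that the choice between averaging 18 items and averaging four dimension means matters. The item weights are 1/18 in the first case and 1/16 or 1/20 in the second, so the two totals would be nearly identical. Nor can it be said that the registry entry needs changing, because it was not seen.

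**Conclusion.** The point holds as a gap in the definition of the primary endpoint. One score and one comparison are promised, while only dimension scores, four unranked visits and several kinds of test are described. As written, the 5% level and 80% power cannot be attached to any identified comparison.

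The inflation is conditional: it arises only if any dimension or any visit could be taken as success. On that condition, with correlations of 0.5 to 0.7, the risk is about 13–16% when either the dimensions or the visits are open. It is about 30–44% when the four disease dimensions and all four visits are open. The second range is an upper scenario, because a repeated-measures test would lower it. The size rests on assumed correlations; that each scenario exceeds 5% does not depend on the exact value within that range.

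**What to change.** State in the protocol:

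- **Score:** one overall CRFK score, for example the mean of the 18 items on the 1 to 5 scale.
- **Time:** one primary time point, for example 4 weeks, the end of the WhatsApp intervention. Alternatively, state explicitly that the repeated-measures group-by-time test is primary.
- **Contrast:** one between-arm comparison, adjusted for the baseline CRFK score that is already collected, at two-sided 5%.
- **Sample size:** rewrite section 3.10 so that the difference and standard deviation refer to that score and that contrast.
- **Everything else:** the other visits are secondary, and the disease and thematic scores are reported as estimates with confidence intervals.

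The particular score and visit are the sponsor's choice, provided that they are fixed before the data are seen. If the Supplementary Materials already define a total, the article should cite that definition in section 3.8. The change needs no new data and no extra participants. The small downside is that dimension-level and later-visit results can no longer be claimed as primary success.
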